### Randomization and blinding

Intra-operatively, the treating surgeon judges whether the patient is eligible for definite inclusion. Prior to formation of the temporary loop ileostomy, loop or split colostomy, included patients will be randomized. Patients will be randomized in a 1:1 fashion to the C-Qur™ Film arm (treatment arm) or the control arm. The randomization will be stratified by operative technique (open or hand-assisted laparoscopy). The allocation sequence will be computer-generated through the web-based program Alea©. A researcher who does not participate in the data analysis will manage the randomization process. This way, the researcher who will perform the data analysis is blinded from treatment allocation. Concealment of treatment allocation and blinding of the surgeon performing the index procedure is not possible because the patient will either get the intervention or does not get an intervention at all. Randomization will be noted in the operation reports, allocation will not.

The patient and doctor at the surgical ward who will complete the case report form during the post-operative period is blinded from treatment allocation. To achieve blinding during the data collection of outcome parameters, the surgeon who will perform the ostomy takedown procedure, will not be the same surgeon as the one who performed the index procedure. Because of the absence of clinical notes regarding allocation, however, the initial surgeon is allowed to do the ostomy takedown in case of man-power or organizational problems.

During the postoperative period after the ostomy takedown, the physician at the ward, who will collect the data regarding the post-operative parameters, will be blinded from the treatment allocation of the patient. The patient will stay blinded for the received treatment.

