### Statistics

In general, for continuous variables, the mean, standard deviation, median, IQR, minimum and maximum values will be presented. Groups will be compared using the *t*-test or Mann-Whitney *U* test, as appropriate, based on the distribution of the data. For categorical variables, the frequencies and percentage within each category will be calculated. Groups will be compared using the chi-square or Fisher’s Exact test, as appropriate, based on the expected counts. All available data will be summarized. Demographics, preoperative, perioperative, and postoperative parameters will be reported and compared for both groups. Descriptive statistics will be presented to describe the trial results. Missing data will be evaluated by the investigators, and appropriate action will be undertaken*.* In case of skewed baseline data between groups, results will be corrected for this data.

Our primary analysis will focus on the effectiveness and safety of the C-Qur film between the treatment group and the control group. A chi-square or Fisher’s Exact test will be performed to assess a significant improvement in the incidence, on the Zühlke score of adhesions underneath the incision site, underneath the loop ileostomy or loop/split colostomy site, and for the extent of adhesions underneath the loop ileostomy or loop/split colostomy site as well. The extent of adhesions underneath the incision site and the time needed for takedown of the ileostomy or loop/split colostomy will be compared using a *t*-test. To assess the safety of the C-Qur film the total incidence of postoperative complications will be compared using a *t*-test or a Mann-Whitney *U* test. The mortality and the incidence for each separate complication will be compared using a chi-square or Fisher’s Exact test.

Subgroup analysis will be performed on laparoscopic versus open colorectal resection, and on ileostomy versus colostomy for the incidence, extent and severity of adhesions as described above. Since data collection of the outcome parameters is not blinded when the same surgeon who performed the index procedure also takes down the ostomy, subgroup analysis will be performed for patients with and without blinded data collection of outcome parameters.

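### Blinded scoring is defined by whether the takedown surgeon is the index surgeon, not by whether the scorer knows the arm, so the blinding subgroup check could falsely reassure

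*Protocol article*

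**What the plan says.** Under Randomization and blinding, the protocol article accepts that "blinding of the surgeon performing the index procedure is not possible", because a patient receives either the film or nothing. It seeks blinded outcome collection by a staffing rule: "the surgeon who will perform the ostomy takedown procedure, will not be the same surgeon as the one who performed the index procedure". It also keeps the arm out of the written record: "Randomization will be noted in the operation reports, allocation will not". There is one exception: "the initial surgeon is allowed to do the ostomy takedown in case of man-power or organizational problems", justified as follows: "Because of the absence of clinical notes regarding allocation".

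The Statistics section returns to the matter: "Since data collection of the outcome parameters is not blinded when the same surgeon who performed the index procedure also takes down the ostomy", and for that reason "subgroup analysis will be performed for patients with and without blinded data collection of outcome parameters".

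Three other places bear on the point. The Design and Control arm sections state that no placebo is used. Data recording and follow-up has the surgeon at takedown pass a laparoscope through the ostomy site and score adhesions at the incision, which is the primary outcome. Design says that the surgeons who perform the index procedures are trained both in placing the film and in mapping adhesions.

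**The concern.** What makes a scorer unblinded is knowledge of the arm. The plan uses a stand-in for it: being the surgeon who performed the index operation. The two differ for any other surgeon who was in theatre after allocation and later does the takedown. That person satisfies the staffing rule and knows the arm. Leaving the allocation out of the operation report does not blind someone who saw the film placed, or saw that none was.

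The primary outcome is a visual present-or-absent judgement, and the lowest positive Zühlke grade is a filmy adhesion that separates easily. Knowledge of the arm could move such a call. The subgroup analysis by blinding status is the only check on this that the article states. If informed scorers sit on its blinded side, the two subgroups become more alike, and their agreement would be read as reassurance that it does not give.

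**Working it through.** **The plan's own figure.** The point disputes no stated number. With 94% against 64% adhesions, two-sided alpha 0.05 and 32 evaluable patients per arm, exact enumeration of Fisher's test gives 80.9% power, in line with the stated 80%. Dropout of 25% gives 32 / 0.75 = 42.7, so 43 per arm and 86 in total, close to the stated 84. None of this changes.

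**The criterion, case by case.**

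| Takedown surgeon | Meets the staffing rule? | Class on the natural reading | Knows the arm? |
|---|---|---|---|
| Performed the index operation | No (exception allowed) | Not blinded | Yes |
| Another surgeon, not present after allocation | Yes | Blinded | Not from the operation |
| Another surgeon, present after allocation | Yes | Blinded | Yes |

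The third row is the gap. The article does not mention this person. Overlap is plausible because placing film and mapping adhesions are taught to the same surgeons, but its frequency is not given.

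**Effect on the subgroup check (illustration).** Assume no true film effect, 94% true adhesions, and aware scorers who call a share *b* of film-arm adhesions absent. Let *g* be the share of film patients in the nominally blinded subgroup whose scorer is in fact aware.

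- Film rate recorded in the unblinded subgroup: 0.94 × (1 − b)
- Film rate recorded in the nominally blinded subgroup: 0.94 × (1 − g·b)
- Gap available to reveal the bias: 0.94 × b × (1 − g)

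With b = 0.20, the gap is 0.94 × 0.20 = 18.8 points when g = 0. It is 18.8 × 0.75 = 14.1 points when g = 0.25, and 18.8 × 0.5 = 9.4 points when g = 0.5. Misclassification shrinks the signal in proportion to *g*. The sizes of the two subgroups are not given, so the chance of detecting the gap cannot be computed.

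**Effect of biased scoring on the overall test (range only).** Inputs: 32 per arm, true rate 94% in both arms, and a share *f* of all film patients scored by someone aware who calls a share *b* of adhesions absent, always in the film's favour. The recorded film rate is 0.94 × (1 − f·b). The test is chosen by expected counts, as in the Statistics section. The cut-off is assumed to be 5, with uncorrected chi-square above it and Fisher below it. Exact enumeration gives:

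| f | b | Recorded film rate | Planned rule | Fisher only | Chi-square only |
|---|---|---|---|---|---|
| 0 | – | 94.0% | 0.36% | 0.33% | 4.0% |
| 0.10 | 0.10 | 93.1% | 0.5% | 0.5% | 4.6% |
| 0.30 | 0.10 | 91.2% | 1.2% | 1.1% | 6.9% |
| 0.25 | 0.20 | 89.3% | 2.7% | 2.3% | 10.6% |
| 0.50 | 0.20 | 84.6% | 11.6% | 9.6% | 24.3% |
| 0.50 | 0.30 | 79.9% | 28.2% | 23.5% | 41.4% |

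For example, f = 0.50 and b = 0.20 give 0.94 × (1 − 0.10) = 0.846. The planned-rule column is the relevant one. At 94% in both arms the expected no-adhesion count is 32 × 0.06 = 1.9 per arm, so Fisher's test would usually apply.

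**The case against.** The Statistics section says when scoring is not blinded. It does not say that scoring is blinded in every other case, so an assistant known to be aware could be classed as unblinded without breaching the text. This is literally true. But the staffing rule is presented as the means of achieving blinding, and no other criterion is offered, so the identity test remains the natural reading.

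The overlapping surgeon is a possibility brought to the text. No assistant is mentioned, and a roster rule or an awareness box may exist in the full protocol or case report form, which are not shown. This stands as a limit: one cannot conclude that awareness is never recorded, nor that informed scorers will be common. It does not remove the point, because the article does state a classification criterion, and that criterion rests on the wrong variable.

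Two stronger readings are tempting and fail. A reader might infer that such scores are treated as blinded in the primary outcome. They are not: the primary comparison is film against control, uses no blinding class, and includes even the admitted same-surgeon scores. A reader might also take 12% or 28% as the trial's false-positive rate. Those figures need half of the film takedowns to be scored by an aware surgeon who errs in one direction only. Smaller inputs stay below the nominal 5%, and reclassification would not alter any of these figures.

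Finally, the plan already takes precautions: a different surgeon by default, no allocation in the operation report, and a subgroup check. That is fair, and it is why the severity is low.

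**Conclusion.** The point holds as a cheap improvement of minor severity. The blinded and unblinded classes rest on index-surgeon identity alone, whereas the bias in question comes from knowing the arm. A takedown surgeon who was present after allocation would, on the natural reading, be placed in the blinded subgroup, and agreement between the subgroups could then reassure falsely.

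The size is unknown because the overlap between index-operation staff and scorers is not given. Under the stated assumptions, the gap that the subgroup check could reveal falls in proportion to the share misclassified. The false-positive rate of the overall test under biased scoring runs from about 0.5% to 28%. Sample size, power and alpha are unaffected.

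**What to change.** Three changes:

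1. On the takedown form, before the laparoscope is introduced, the scorer records whether he or she attended the index operation after allocation or otherwise knows the arm. Completing it before takedown starts would also cover the ostomy-site scores, which are made earlier.
2. In Statistics, define blinded data collection by that recorded answer, not by index-surgeon identity alone.
3. In Randomization and blinding, extend the preference for a different surgeon to anyone present after allocation, where rostering allows and under the existing staffing exception.

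The cost is one item on the form, two sentences of wording and some checking of rosters. No extra assessor or procedure is needed. The downside is that the truly blinded subgroup may be smaller. Changes 1 and 2 make the check honest. Only change 3 can reduce the bias itself. The Trial status section says inclusion has not started, so all three can apply from the first patient.

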### Analysis and sample size

It is hypothesized that the use of the C-Qur™ Film underneath the primary incision reduces the incidence of adhesion at the incision by 30%. This hypothesis is based on the supporting documentation for Seprafilm™ (treatment) versus Control (no treatment) with an adhesion rate of 94% in the control group and 64% in the treatment group [18–22]. We estimate a total drop out of 25% in this study, comprising 10% regular drop out and 15% drop out because of anastomotic leakage. A 15% drop out because of anastomotic leakages is chosen because it is the upper limit of the incidence of this complication. Assuming that the C-Qur™ Film group performs similarly to Seprafilm™, a total of 84 patients, (32 + 10 per group (25% drop out)) would be needed in a randomized study, with 80% power and two-sided alpha = 0.05 in order to detect a 30% reduction in incidence of adhesions.

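### The planned subgroup analyses contain no estimate of how the film effect differs between levels, so they cannot show whether technique, ostomy type or unblinded scoring changes it

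*Protocol article*

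**What the plan says.** The Statistics section sets out two-arm comparisons of film against control. For adhesion incidence, a chi-square or "Exact test will be performed to assess a significant improvement in the incidence". The same tests serve the Zühlke score and the extent of adhesions at the ostomy site. A t-test serves extent under the incision and takedown time.

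Subgroup analyses follow for three two-level factors:

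- **Technique and ostomy type.** These are analysed by laparoscopic versus open resection and "on ileostomy versus colostomy for the incidence, extent and severity of adhesions as described above". The closing words refer back to the two-arm tests.
- **Blinding of scoring.** Outcome collection is unblinded when the index surgeon also takes down the ostomy, so "subgroup analysis will be performed for patients with and without blinded data collection of outcome parameters". No test is named.

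Two of these analyses have a stated purpose. The blinding analysis is justified by the possibility of unblinded scoring. The Discussion says the technique analysis is meant to control for the difference in surgical technique. No treatment-by-subgroup estimate appears anywhere in the article, and no subgroup analysis is labelled exploratory. The only significance level is in the sample-size statement, "with 80% power and two-sided alpha = 0.05 in order to detect a 30% reduction in incidence of adhesions", which concerns the overall comparison.

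**The concern.** A film-versus-control test run inside a subgroup asks whether the film works in that level. It does not ask whether the film works differently in the two levels, which is the question a subgroup analysis is normally meant to inform. The blinding analysis clearly asks that second question: if unblinded scoring biases the outcome, the apparent film effect should differ between patients scored blind and patients scored by the index surgeon. Two separate p-values do not address this. Nor do separate tests by technique adjust the overall comparison for technique.

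The trial is sized for one comparison of about 32 against 32. Each level has much less power, so one level can easily be significant and the other not when the true effect is the same in both. With no between-level estimate on the page, a reader has only the pair of p-values to compare. At stake are the interpretation of the subgroup results and the only analytic check the article offers on unblinded scoring of the primary outcome.

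**Working it through.** **Inputs from the protocol article**

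- Rates: "with an adhesion rate of 94% in the control group and 64% in the treatment group" (Analysis and sample size).
- Size: "a total of 84 patients, (32 + 10 per group (25% drop out)) would be needed" (same section), so 32 evaluable per arm.
- Allocation: "Patients will be randomized in a 1:1 fashion to the C-Qur™ Film arm (treatment arm) or the control arm" (Randomization and blinding).
- Stratification: "The randomization will be stratified by operative technique (open or hand-assisted laparoscopy"; ostomy type and blinding status are not stratified.

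**Assumptions**

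- The article gives no subgroup shares. I split the 32 per arm as 16/16, 20/12, 24/8 and 27/5, balanced between arms.
- I use a two-sided 5% level within each level, because no subgroup level is stated.
- The same 94% versus 64% holds in both levels, so there is truly no subgroup difference.

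**Step 1: the plan's own figure.** Full binomial enumeration of Fisher's exact test at 94% versus 64% gives power 0.790 with 31 per arm and 0.809 with 32. So 32 is the smallest size reaching 80%, and the plan's figure is reproduced.

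**Step 2: discordance when the effect is identical.** Let A and B be the exact power in the two levels. Then

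P(exactly one significant) = A(1 − B) + B(1 − A).

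Two test rules were enumerated: chi-square throughout, and chi-square replaced by Fisher when an expected count is below 5. The last column comes from unrounded powers.

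| Split per arm | Rule | A | B | P(exactly one significant) |
|---|---|---|---|---|
| 16/16 | chi-square | 0.601 | 0.601 | 0.479 |
| 16/16 | chi-square/Fisher | 0.442 | 0.442 | 0.493 |
| 20/12 | chi-square | 0.694 | 0.423 | 0.530 |
| 20/12 | chi-square/Fisher | 0.615 | 0.252 | 0.557 |
| 24/8 | chi-square | 0.785 | 0.231 | 0.653 |
| 24/8 | chi-square/Fisher | 0.747 | 0.081 | 0.707 |
| 27/5 | chi-square | 0.839 | 0.186 | 0.713 |
| 27/5 | chi-square/Fisher | 0.784 | 0.045 | 0.759 |

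Worked case, 24/8 with chi-square/Fisher: 0.747 × 0.919 + 0.081 × 0.253 = 0.687 + 0.020 = 0.707.

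**Step 3: the same probability with no film effect.** Over splits from 16/16 to 29/3 and both rules, it is 0.2–3.6% if both arms are at 94%, and 4.6–11% if both are at 64%.

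**Step 4: what a between-level estimate would deliver.** For the difference of risk differences with n₁ and n₂ per arm in the two levels,

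SE = √(v/n₁ + v/n₂), where v = 0.94 × 0.06 + 0.64 × 0.36 = 0.0564 + 0.2304 = 0.2868.

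| Split per arm | SE | 95% CI half-width (1.96 × SE) | Difference detectable with 80% power (2.8 × SE) | Power for a 30-point difference |
|---|---|---|---|---|
| 16/16 | 0.189 | 37 points | 53 points | 35% |
| 24/8 | 0.219 | 43 points | 61 points | 28% |
| 27/5 | 0.261 | 51 points | 73 points | 21% |

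Under the equal effects of step 2, simulation of this comparison gives a false difference in 3.3–3.6% of trials with Newcombe-type score intervals (16/16, 20/12 and 24/8). A simple Wald test gives 6.6% at 16/16 and 8.2% at 24/8. The excess over 5% is the reason to prefer a score-based interval.

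**The case against.** The strongest reply is that this is a journal article, and interaction tests, hierarchy and exploratory labels are commonly left to the full protocol or analysis plan. That stands as far as missing detail goes, and an unseen plan may already contain the estimate. But the article does more than stay silent. For technique and ostomy type it fixes the method by pointing back to the two-arm tests. For blinding and technique it states a purpose that within-level tests cannot serve.

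Several stronger readings are tempting, and the documents do not support them:

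- **That the subgroup tests are run at a full 5%.** No subgroup level is stated; 0.05 belongs to the sample-size statement. The level is not the cause either. The discordance comes from low power within levels and from not estimating the difference, so a stricter level would not cure it.
- **That the blinding analysis reuses the two-arm tests.** This is an inference, since no test is named for it.
- **That the plan will usually report a false difference.** Discordance exceeds one half only if the film works as planned and the split is uneven, and no split is given. The article also never says that discordant p-values will be read as a difference.
- **That an ineffective film would produce spurious subgroup positives far above 5%.** For incidence with both arms at the plan's 94%, six within-level tests give at least one in only about 2% of simulated trials. It reaches 12–17% only at true rates of 50–79%.
- **That an interaction by blinding status would settle scoring bias.** Unblinded takedown arises after randomization, for staffing reasons. A difference could not be attributed to unblinding alone.

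It is also fair to say that the between-level estimate will be imprecise. That limits what can be claimed, but a wide interval at least shows the limit, which two separate p-values do not.

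**Conclusion.** The point holds in a limited form. The article names no estimate of how the film effect differs between levels for any of its three subgroup factors, and separate within-level tests cannot show whether it does. If the film has the planned effect equally in both levels, with 32 evaluable per arm, exactly one level would be significant in about 48–49% of trials at an even split, 53–56% at 20/12 and 65–71% at 24/8. With no film effect this falls to at most about 11%. These figures rest on assumed, arm-balanced splits and an assumed 5% level within subgroups. They describe a risk of misreading, not a stated decision rule. The primary outcome and its overall test are untouched.

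**What to change.** In the Statistics section, replace the reference back to the two-arm tests with a rule covering all three factors:

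- Report the film-control difference with a 95% confidence interval in each level.
- Report the between-level difference in that effect (the treatment-by-subgroup interaction) with its interval. For incidence, use the difference of risk differences with a score-based interval.
- Report no film-control p-values within levels.
- Label all subgroup analyses exploratory.
- For blinding of scoring, present the interaction as evidence consistent with or against scoring bias, not as proof, because blinding status is not randomized.

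If an analysis plan already says this, the article's wording need only be aligned with it. The cost is a few sentences and trivial extra analysis, with no added patients. The Trial status section says inclusion has not started, so the rule can be fixed before any data exist. The downside is low precision: only between-level differences of about 53 points or more would be detectable with 80% power, so the trial could support no subgroup-specific claim.

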### Reporting

The CLIPEUS trial findings will be reported in concordance with the Consolidated Standards of Reporting Trials (CONSORT) checklist [23].

## Discussion

Results of this study add to the evidence on the use of anti-adhesive barriers in open and laparoscopic ‘hand-assisted’ colorectal surgery. Although the ultimate objective of adhesion prevention is to reduce the clinical consequences of adhesions, we chose incidence of adhesions to the incision site as primary outcome measure. Clinical outcomes such as small bowel obstruction, secondary infertility and adhesiolysis related complications are considered multifactorial and difficult to interpret [24]. Incidence of adhesions at repeat surgery is believed to be the most valuable surrogate endpoint for clinically relevant adhesion prevention, since small bowel obstruction and adhesiolysis at repeat surgery are not likely to occur when complete adhesion reduction in a patient is accomplished. No adhesion under the incision site in particular will benefit patients at re-laparotomy or re-laparoscopy. Recent evidence from our group emphasizes the large disease and socioeconomic burden of adhesions needing lysis at subsequent abdominal surgery [5].

To be able to evaluate incidence of postoperative adhesions, a second-look surgery model is required, also because noninvasive methods such as cine-magnetic resonance imaging (MRI) have not been validated measuring adhesion reduction [25]. Colorectal resection with temporary loop ostomy is an obvious choice, since colorectal surgery is frequently performed and known for its relatively high incidence of adhesion-related complications [26]. We will include patients undergoing resection for benign or malignant indication. Malignancy is the largest indication for colorectal resection, and since (disease-free) survival has strongly increased, life time risk of adhesion-related complications has increased correspondingly.

In this study, both laparoscopic and open colorectal resections will be included. In many countries, laparoscopic colorectal resection for benign and malignant diseases has gained popularity [27]. Thus, performing only an open colonic resection study would lower the generalizibility of the results on adhesion prevention. Laparoscopic technique is accompanied by less tissue trauma. Hence, it is suggested that laparoscopic colorectal surgery results in fewer adhesions. A recently published population-based register study specifically addressed readmission rate for clinically apparent adhesions after colorectal surgery, comparing the open and laparoscopic approach [28]. Of the total of 187,148 patients included, 11,013 (5.9%) had laparoscopic resection. With a median follow-up of 31.8 months, overall adhesion-related readmission rate was 8.1%; 8.2% after an open approach versus 6.3% after a laparoscopic approach (*P* <0.001). An important limitation of this study was the higher percentage of emergency operations in the open group compared to the laparoscopic group. The most common underlying disorder for an emergency laparotomy (that is, peritonitis) has a higher adhesion formation propensity. Despite the relative reduction of 23% in the re-admission rate, it should be concluded that clinically relevant consequences of adhesions are substantial also after laparoscopic surgery. A subgroup analysis for open versus laparoscopic resection will be conducted to control for the difference in surgical technique and concomitant adhesion formation.

For the sake of safe and secure placement of the adhesion barrier, only patients undergoing laparoscopic resection with a specimen extraction incision of at least 6 cm will be included in our study. This minimal incisional length was chosen based on previous experience with the C-Qur™ Film. The availability of different sizes of the film and the tissue adherence only at one site improve the placement in narrow spaces. These characteristics provide potentially better handling when compared to the commonly used HA/CMC barrier film in open colorectal surgery.

